#### Intervention Development.

We will develop phenotype-specific neuropsychological rehabilitation plans targeting the predominantly affected cognitive domains as uncovered in Workstream 1, with methods informed by past work on use of neuropsychological rehabilitation to alleviate cognitive deficits arising from CNS infection. To allow for anticipated heterogeneity in the severity and range of cognitive impairment in people with long Covid, different types of cognitive intervention will be employed, including remediation techniques (e.g. improving attention by lengthening the time to complete simple tasks), compensatory and adaptive strategies (e.g. use of memory notebooks and mnemonics). Our neuropsychological rehabilitation plans for Covid-19 will follow the 2013 NICE guidelines on Stroke rehabilitation (section 1.4. Cognitive functioning), 2013 SIGN guidelines on Brain Injury Rehabilitation and evidence

provided by recent systematic reviews SIGN advises on the approach to address the rehabilitation of memory, attention and executive function and recommends the use of therapies such as meta-cognitive strategies (e.g. problem-solving, goal-management and strategic reasoning to treat executive dysfunction, task-specific training for attentional deficits and the use of external aids (e.g. digital diaries) and internal strategies (e.g. use of visual imagery) for mild-moderate memory problems. Likewise, the NICE guidelines recommend that attention training is focused on relevant functional tasks and training on the use of internal strategies to encode information to treat memory problems, as well as environmental strategies (e.g. environmental prompts) and use of external aids. The goal of the intervention trialled in WS2 is to reduce disability due to 'cognitive Covid' and restore a level of function as similar as possible to level pre-infection.

The interventions will be delivered in 10 individual sessions of 1 hour duration over a period of 3 months (1 session per week approximately). In the first session relevant goals will be identified, alongside with a suite of strategies adjusted to the individual needs based on: 1) existing strategies already tried by the individual and found successful, 2) information from WS1 about the individual's profile of cognitive impairment (e.g. dominant dysexecutive function vs dominant amnesic impairment) and 3) personal preferences.

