### **4.4 COMPLIANCE/ADHERENCE**

There is no planned analysis for compliance and treatment adherence. Sensitivity analysis will be run on the number of intervention sessions received, see section 6.9 for further details.

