## 4.5 PROTOCOL VIOLATIONS

Definition of protocol violations and deviations. Violation is an intended failure to adhere to the protocol such as wrong treatment being prescribed or administered or incorrect data being collected and documented. A protocol deviation is an unintended failure to adhere to the protocol and examples include errors in applying inclusion/exclusion criteria or missed follow-up visits due to error. Protocol deviations and violations will be monitored and detailed descriptively in the analysis report. If protocol deviation occurrences rise above 10% then sensitivity analysis as detailed in section 6.5 will be conducted. Some examples of protocol deviations which might occur in this study include;

- Patients not receiving randomised allocation.
- Ineligible participants being randomised.
- Participants receiving their BGSi goals after completing it at baseline.

*ITT is the expected standard for RCTs and demonstrates the effectiveness of the intervention in the pragmatic context. Per protocol will provide evidence of efficacy and if there is a large difference then there may be a difficulty in implementation of the intervention which needs fixing before the intervention would be adoptable by the NHS.*

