## **6.9 SENSITIVITY ANALYSES OR MODEL TESTING**

If MI is used, then complete case analysis will be run to evaluate any impacts that MI has had on the results. This will be done on the primary outcome (BGSi attainment at 3 months) and any secondary outcomes that are statistically significant with MI analysis.

A sensitivity analysis will be run for the number of intervention sessions attended\*; this will be run by including number of sessions in the analysis model (as a continuous variable) along with the interaction with group.

An additional sensitivity analysis will be conducted on the primary outcome (BGSi attainment at 3 months) to assess impact of intervention treatment windows\*. Along with including number of sessions in the model as above, participants who did not receive the intervention within the correct window for any one session will be excluded (not including missed sessions).

*\*Presented in unblind report once all primary analysis listed in this SAP is complete.*

Sensitivity analysis will be conducted on the primary outcome (BGSi attainment score) at 2 and 6 months only including the participants whose data was collected within the aimed timeframe, that is within 2 weeks of the follow up due date.

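### The SAP 6.9 session model includes an interaction that duplicates the session term; once one is dropped, its group coefficient is a zero-session contrast, and the window analysis is not a randomised comparison

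*Combined protocol and SAP*

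**What the plan says.** SAP 4.4 states "There is no planned analysis for compliance and treatment adherence" and refers the reader to 6.9. There, "A sensitivity analysis will be run for the number of intervention sessions attended", by "including number of sessions in the analysis model (as a continuous variable) along with the interaction with group". A further analysis of treatment windows follows. "Along with including number of sessions in the model as above", it adds that "participants who did not receive the intervention within the correct window for any one session will be excluded", missed sessions not counting. Both are reserved for the unblinded report, after the primary analyses.

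The sessions belong to the rehabilitation programme. Protocol 5.2.2 (Intervention Development) says "The interventions will be delivered in 10 individual sessions of 1 hour duration over a period of 3 months". Under protocol 5.2.2.1 the comparator is standard of care, and the only rehabilitation contact offered to controls is a workshop after data collection ends.

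Two related statements:
- SAP 4.5: "If protocol deviation occurrences rise above 10% then sensitivity analysis as detailed in section 6.5 will be conducted". Section 6.5 is descriptive statistics.
- SAP 6.9: "Sensitivity analysis will be conducted on the primary outcome (BGSi attainment score) at 2 and 6 months", restricted to data collected within two weeks of the due date. SAP 5.2 has outcomes at baseline, 3 and 6 months.

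**The concern.** An interaction with group asks whether the session slope differs between arms. Controls have no sessions, so they have no slope to compare. The SAP does not say what session value controls take, whether sessions are centred, which of the collinear terms is kept, or which coefficient will be reported. An analyst who follows the text gets a dropped term and a group coefficient that looks like a treatment effect but refers to people allocated to rehabilitation who attended none of it.

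Sessions attended are also a post-randomisation variable. If people with a better course attend more, the slope absorbs prognosis and the group coefficient moves the other way. A table headed as a sensitivity analysis could then appear to contradict a real benefit.

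The window analysis has the same term and a second problem. Controls cannot have an out-of-window session, so only the intervention arm is trimmed.

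**Working it through.** **Inputs**
- Effect 0.7, two-sided 5%, 90% power, 44 per arm analysed: SAP 4.1 and 4.3.
- SD 2.86 points, from 2 / 0.7: protocol, Power calculation.
- Sessions from 0 to 10 in the intervention arm: protocol 5.2.2.
- Controls at 0 sessions: inferred from protocol 5.2.2 and 5.2.2.1, not stated.
- Mean and SD of sessions attended, and the correlation of attendance with prognosis: not in the documents. These are assumed and varied.

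**The plan's own figure.** The two-sample t-test calculation gives 43.87, so 44 per arm and 88 in total, with power 0.901. Then 88 / 0.75 = 117.3, so 118. The sample size reproduces and is not in question.

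**Step 1: rank.** Write G for group (0/1) and S for sessions. In controls S = 0 and G×S = 0. In the intervention arm G×S = S. The columns S and G×S are therefore identical, and [1, G, S, G×S] has rank 3 of 4. It has rank 2 if every intervention participant attends the same number.

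**Step 2: what the group coefficient means.** With one of the two columns dropped, E(Y) = a + bG + cS. The coefficient b is the contrast at S = 0. With mean attendance m, the ITT difference is b + c×m, so b equals it only if c = 0.

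**Step 3: precision of b.** With n per arm, and s the SD of sessions:

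Var(b) = σ²[2/n + m²/(n s²)], against σ²(2/n) without the session term. The SE ratio is √[1 + m²/(2s²)].

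- 7/3: √(1 + 49/18) = 1.9
- 8/2: √(1 + 64/8) = 3.0
- 9/1.5: √(1 + 81/4.5) = 4.4

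In points, 2.86 × √(2/44) = 0.61 without the term, and 3.0 × 0.61 = 1.83 at 8/2. Both variances leave out the other covariates in 6.6.

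**Step 4: bias when attendance tracks prognosis.** Let ρ be the correlation of sessions with the untreated outcome, and let the true effect be a constant 2.0. The slope c is then about ρ × 2.86/2 = 1.43ρ, so b is about 2.0 - 8 × 1.43ρ = 2.0 - 11.44ρ. Simulating whole sessions capped at 10 shrinks the session SD and steepens this:

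| ρ | formula, uncapped | simulated mean of b |
|---|---|---|
| 0.1 | +0.86 | about +0.7 |
| 0.2 | -0.29 | about -0.5 |
| 0.3 | -1.43 | about -1.7 |
| 0.5 | -3.72 | about -4.2 |

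Repeat simulations agree to about 0.1. The plain group difference stayed at 2.0 in every row.

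**Step 5: centring.** Replace S by S - m in the intervention arm and keep 0 in controls. The model then has full rank and b is again the ITT-type difference, with SE 0.213σ, the same as without the session term.

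**Step 6: text comparison.** The window rule can remove people from one arm only, on behaviour after randomisation, and neither document's text defines the correct window. SAP 4.4 plans no adherence analysis, yet protocol 7.3 says one is detailed in the SAP, and SAP 4.5 says a per-protocol analysis will give evidence of efficacy. The 4.5 pointer leads to a section with no such analysis. No 2-month visit exists.

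**The case against.** The best defence is that little depends on these models. They are labelled sensitivity analyses, run after the primary ITT analysis and reported separately. That stands, and it limits the severity.

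It is also true that dropping the redundant column leaves an estimable session slope within the intervention arm, which may be all the authors wanted. A reader might infer that the whole session analysis cannot be run. That goes too far: only an interaction separate from the session term is lost. The SAP also never says that the group coefficient will be read as the treatment effect.

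Zero sessions for controls is an inference. SAP 4.5 lists failure to receive the allocated arm as a possible deviation, and a few crossovers would make the interaction formally estimable, but only from those few people. If some intervention participants attend nothing, zero lies at the edge of the data rather than beyond it. The coefficient still does not estimate the ITT effect.

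A reader might also infer that the trial loses power, or that the model would give a large negative effect. The documents support neither. The powered comparison is the primary model, which has no session term. A value near -4.2 needs an attendance-prognosis correlation of about 0.5, and the documents give no such figure.

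Finally, the direction of any bias from the window exclusion is unknown, since late sessions may reflect therapist scheduling.

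**Conclusion.** The concern holds, as a should-fix. The duplicated column is exact algebra once controls have zero sessions. The uncentred group coefficient is then a zero-session contrast. Its SE is 3.0 times that of the plain comparison at assumed attendance 8/2 (1.9 to 4.4 over 7/3 to 9/1.5), and under the step 4 assumptions its average changes sign between correlations of 0.1 and 0.2. The size depends on those assumed attendance figures; the defect does not.

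The window analysis carries the same term and is not a randomised comparison. The 6.5 pointer, the 2-month timepoint and the conflicting statements on adherence analysis are plain inconsistencies. The ITT primary analysis and the sample size are untouched, so the documents do not support a must-fix rating.

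**What to change.** 1. In SAP 6.9, drop the sessions-by-group interaction. If a session slope is kept, centre sessions at the intervention-arm mean with controls set to 0, and label the slope a non-randomised within-arm association.
2. If an adherence-adjusted effect is wanted, use two-stage least squares with sessions received (0 for controls) instrumented by allocation and the 6.6 covariates. State two assumptions with the result: allocation acts only through sessions, which is open to question when participants are unblinded and rate their own goals; and the effect is linear per session, which any scaling to 10 sessions needs. Do not use in-window sessions as the exposure, because out-of-window sessions can also act. With an assumed 0.25 points per session and 70% in window, the estimate would be 0.25 / 0.7 = 0.36 per session.
3. Label the window analysis non-randomised and descriptive and define the window, or remove the analysis.
4. Point SAP 4.5 to a section that specifies the deviation or per-protocol analysis. Keep it separate from the session analysis, since an adherence-adjusted effect does not deal with ineligible participants or with goals disclosed after baseline. Reconcile SAP 4.4 with SAP 4.5 and protocol 7.3.
5. Change the 2-month timepoint in 6.9 to 3 months.

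The cost is SAP wording and at most one extra model on data already collected. Settle it before unblinding, so that the choice of term and coefficient is not made with results in view.

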#### 5.2.2.1 Trial design

This will be an individually randomised parallel group controlled trial, comparing the study intervention (cognitive rehabilitation) with the clinical standard of care (current clinical management pathways for long Covid, including treatment for fatigue, respiratory disorders, sleep, anxiety and depression).

590

591 5.2.2.2 Participant flow

592

593 Post-consent participants will undergo baseline assessment before randomisation to receive  
594 either neuropsychological rehabilitation or treatment as usual.

595

596 5.2.2.3 Outcome measures

597

598 The primary outcome will be participant-reported goal attainment at 3 months post-  
599 randomisation. This will also be collected at the 6 month post-randomisation follow up. This  
600 will be collected using the Bangor Goal Setting Interview (BGSi).

601

602 Secondary outcomes will be:

- 603 • Cognitive function (tested using the cognitive batteries employed for Workstream 1)
- 604 • Quality of life (EQ-5D-5L)
- 605 • Life Space Assessment
- 606 • Social Functioning (SF-DEM)
- 607 • Instrumental Activities of Daily Living (IADL) Scale
- 608 • Generalised Anxiety Disorder Assessment (GAD-7)
- 609 • Patient Health Questionnaire (PHQ-8)
- 610 • Chalder Fatigue Scale
- 611 • Pittsburgh Sleep Quality (PSQI)
- 612 • DePaul Symptom Questionnaire – Post-Exertional Malaise (DSQ-PEM).
- 613 • Client Service Receipt Inventory (CSRI)

614

615 5.2.2.4 Health economic analyses

616

617 From a public sector, multi-agency perspective we will conduct an economic evaluation to  
618 determine the incremental cost-effectiveness of the intervention in comparison to clinical  
619 standard of care. The intervention of interest will be a novel neuropsychological rehabilitation  
620 intervention programme for cognitive Covid compared to clinical standard of care (i.e. current  
621 clinical management pathways for long Covid, including treatment for fatigue, respiratory  
622 disorders, sleep, anxiety and depression). We will examine two research questions during  
623 the economic evaluation:

624

- 625 1. What is the incremental cost-effectiveness of CICERO-Rehab compared to standard  
626 clinical care for cognitive Covid?
- 627 2. What is the cost per QALY of CICERO-Rehab compared to standard clinical care for  
628 cognitive Covid, and does this fall below the NICE threshold of £20,000 to £30,000  
629 per QALY?

630

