## **7.3 Unblinding procedure**

There are no blinding requirements in workstream 1.

Due to the nature of the intervention in workstream 2 participants will not be blinded to the allocation they receive. However, every effort will be made to maintain blinding for the researchers collecting data where logistically possible. The Trial Statistician will be blind to allocation until the quantitative analysis, as detailed in the statistical analysis plan (SAP) has been carried out. Once the blinded results have been shared with the study team and the results discussed and interpreted, the unblinded analysis (as detailed in the SAP) such as adherence analysis will be carried out.

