### 3.3 TRIAL DESIGN

WS2 – The second workstream will develop a suite of phenotype-specific and evidence-based neuropsychological rehabilitation packages targeted at the cognitive domains primarily affected in cognitive Covid, using functional and quality of life outcomes to measure treatment efficacy. This collection of strategies will be informed by outcomes from workstream 1 and co-produced in collaboration with a group of people living with cognitive Covid-19 (we will refer to this group as Experts by Experience). This will be a parallel individually randomised controlled trial, comparing the study intervention (cognitive rehabilitation) with the clinical standard of care (current clinical management pathways for long Covid, including treatment for fatigue, respiratory disorders, sleep, anxiety and depression).

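### The session-count sensitivity model in SAP 6.9 includes a sessions-by-group interaction that cannot be estimated, because only the rehabilitation arm has sessions

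*Combined protocol and SAP*

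**What the plan says.** SAP 6.9 states: "A sensitivity analysis will be run for the number of intervention sessions attended". The method is "including number of sessions in the analysis model (as a continuous variable) along with the interaction with group". The treatment-window analysis in the same section uses the term again: "Along with including number of sessions in the model as above". Both go into the report written after unblinding.

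Sessions belong to one arm. In the protocol's intervention development text, "The interventions will be delivered in 10 individual sessions of 1 hour duration over a period of 3 months". SAP 3.3 describes the trial as "comparing the study intervention (cognitive rehabilitation) with the clinical standard of care", and under protocol 5.2.2.2 participants receive "either neuropsychological rehabilitation or treatment as usual". Controls are offered an online workshop on the strategies, but only once data collection has ended. The SAP does not say what session value a control receives, whether sessions are centred, or which coefficient will be interpreted.

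On adherence more generally, SAP 4.4 says "There is no planned analysis for compliance and treatment adherence" and in its next sentence refers the reader to 6.9 for the session analysis. Protocol 7.3 says that "the unblinded analysis (as detailed in the SAP) such as adherence analysis will be carried out".

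**The concern.** An interaction between sessions and group asks whether the session slope differs between arms. Controls have no variation in sessions, so they have no slope and the question has no answer in the data. The analyst will have to decide, after unblinding, how to code controls, whether to centre, and which term to drop. Those choices decide what the reported group coefficient means.

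The slope that can be estimated comes from the rehabilitation arm alone and uses a variable that arises after randomisation. People who attend more may differ in prognosis. SAP 6.6 adjusts for age, gender, education, baseline RBANS and baseline BGSI, but not for fatigue or post-exertional malaise, which could plausibly affect both attendance and outcome in long Covid.

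At stake is the interpretation of a pre-specified check on the primary result. A group term that shrinks or changes sign once sessions enter could be taken as evidence against the therapy, and a positive slope as evidence of a dose effect.

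**Working it through.** **Inputs from the documents.** Evaluable sample 44:44, d = 0.7, 90% power, two-sided 5%, 25% attrition (SAP 4.1, 4.3). Difference of 2 points, implied SD 2.86, and baseline SD 1.74 in the dementia rehabilitation trial the protocol cites (protocol power calculation). 10 planned sessions.

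**Assumed, because the documents give no value.** The attendance distribution, and the correlation ρ between attendance and outcome prognosis. The simulations include no covariates.

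**1. The plan's own figure.** A two-sample t-test with d = 0.7 needs 43.87, so 44 per arm (power 0.901), and 88 / 0.75 = 117.3, so 118. Both stated figures reproduce, and nothing below changes them.

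**2. Rank.** The design columns are [1, G, S, G×S].
- Controls S = 0: G×S = S for every participant. The largest difference is 0 and the rank is 3 of 4. Subtracting a constant from S for everyone leaves the rank at 3.
- Controls missing: 44 rows remain, all with G = 1. The rank is 2 and the group effect is not estimable.

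**3. Which term is dropped.** Let m be the mean number of sessions in the rehabilitation arm and b the slope.
- Uncentred: S and G×S are identical, so dropping either gives the same fit, with group coefficient = ITT − b × m. This is the contrast at zero sessions.
- Centred at m, interaction dropped: the group coefficient is still ITT − b × m.
- Centred at m, sessions main effect dropped: the group coefficient equals ITT.

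The fitted values are the same in every case. Only the number labelled group changes.

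**4. Size with SD 1.74.** The true effect is 1.2 points for everyone (0.7 × 1.74 ≈ 1.2). Assumed sessions are round(8 + 2.5u) limited to 0–10, with u standard normal, giving mean 7.7 and SD about 2.07.

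At ρ = 0, the SE of the zero-session contrast is 1.74 × √(1/44 + 1/44 + 7.7² / (43 × 2.07²)) = 1.74 × √(0.0455 + 0.3218) = 1.05. For ITT it is 1.74 × √(2/44) = 0.37. The ratio is 2.8 (simulation mean 2.9).

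| Assumed ρ | ITT estimate | Group coefficient at zero sessions | Slope p < 0.05 when there is no treatment effect |
|---|---|---|---|
| 0 | 1.2 | 1.2 | 5% |
| 0.1 | 1.2 | 0.6 | about 9% |
| 0.2 | 1.2 | 0.0 | about 25% |
| 0.3 | 1.2 | −0.6 | about 47% |
| 0.4 | 1.2 | −1.3 | about 72% |

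The SE of the group coefficient is 1.0 to 1.1 throughout. Check at ρ = 0.3: the slope averages 0.238, and 1.20 − 0.238 × 7.70 = −0.63.

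**5. Size with the protocol's 2 points and SD 2.86.** Assumed mean attendance is 7.6.
- Constant effect of 2.0, no confounding: ITT 1.99 (SE 0.61), group 1.95 (SE 1.77).
- Constant effect of 2.0, with an unmeasured trait worth 1.0 to 1.43 points per SD that also raises attendance: ITT 2.0, group −0.85 to −2.05, slope 0.37 to 0.53 per session.
- Benefit of 0.25 points per session, no confounding: ITT 1.90, group −0.01.

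In the last case the therapy works exactly as intended and the group term is null, because it describes someone who attended nothing.

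**The case against.** The strongest reply is that this is a question of parameterisation. Centre sessions at the rehabilitation-arm mean, keep the interaction and drop the main effect, and the group coefficient is the ITT estimate again. The negative values mislead only if someone reads an uncentred main effect as the treatment effect, which SAP 6.9 does not say it will do. That is correct, but it is only a partial rescue: centring while dropping the other term leaves about −0.6, and the SAP specifies neither choice.

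Other points that stand:
- A reader might infer that the analysis cannot run at all. Software drops a term and still returns one usable slope within the rehabilitation arm. What is lost is the separate interaction.
- Zero sessions in controls is inferred from the comparator. SAP 4.5 lists patients not receiving their allocation as a possible deviation, so some crossover is conceivable.
- The size of the bias rests on assumed correlations. At ρ = 0 there is none, and the SAP 6.6 covariates would remove part of any confounding.
- A reader might infer that SAP 4.4 contradicts protocol 7.3. Read with its next sentence, 4.4 points to the session analysis, which is run after unblinding, as 7.3 describes. The difference is largely one of wording.
- A reader might infer that this is the only adherence analysis. SAP 6.9 also has the treatment-window analysis, and 4.5 promises a sensitivity analysis if deviations exceed 10%, although its reference to 6.5 leads to descriptive statistics.
- An instrumental-variable analysis is not an obvious replacement. Without covariates its per-session effect is ITT / m (1.2 / 7.7 = 0.156), which rescales the primary result and does not show whether more sessions help. Its exclusion restriction is debatable when unblinded participants rate their own goals.

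**Conclusion.** The specification is wrong as written and needs correcting. The rank result is algebra and needs only that controls have no sessions. With uncentred sessions, the group term that remains is a contrast at zero sessions: unbiased but about 2.8 to 2.9 times less precise when attendance is unrelated to prognosis and the effect does not depend on sessions, and otherwise displaced from ITT by the slope times mean attendance. The displaced values above illustrate the mechanism under assumed attendance and correlations without covariates. They do not predict this trial. The slope is a non-randomised association with residual confounding of unknown size and direction.

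A reader might go further and conclude that the trial's main result is at risk. The documents do not support that. The ITT model in SAP 6.6 contains no session term, the sample size reproduces, and this analysis runs only after the blinded results have been reported. Severity: should-fix.

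**What to change.** In SAP 6.9:
- Remove the sessions × group interaction and the session term from the two-arm model, both in the session analysis and in the treatment-window analysis that reuses it. The window analysis then compares arms with the SAP 6.6 model after its stated exclusions.
- Report the association of sessions attended with 3-month BGSI attainment within the rehabilitation arm only, adjusted for the SAP 6.6 covariates, and label it non-randomised.
- Optionally add a supportive complier-average (instrumental-variable) analysis, with randomised arm as instrument, sessions 0 in controls and one pre-stated attendance threshold. State the exclusion restriction, and that a threshold version also assumes no effect below the threshold.
- Reword SAP 4.4 so that it names these analyses.

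The cost is about a paragraph of SAP text and no new data. The within-arm slope will be imprecise with about 44 evaluable participants and cannot support a causal dose claim. Any instrumental-variable estimate will have a wide interval.
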